##### Patient/Client Satisfaction Questionnaire (CSQ-8 [30])

At discharge and after 3 and 12 months, patients are asked to complete the German version of the CSQ-8. The CSQ-8 is a unidimensional, 8-item questionnaire assessing patient satisfaction with the rehabilitation. The items are rated on a 4-point Likert scale, ranging from 1 to 4. A higher score indicates higher satisfaction with the rehabilitation program.

##### Rehabilitation goals

Participants are questioned at the beginning of the rehabilitation about the primary goals they want to reach during the course of rehabilitation. Once a week they as well as the therapists are asked to fill out a questionnaire about their satisfaction with goal achievement. Further, they can express if their goals for the following week have changed. These formulated goals will be linked to the ICF categories.

### Semi-structured feedback interview

At the end of the rehabilitation program, a semi-structured feedback interview will be held in which the patients will be asked to describe their experiences with the rehabilitation program by a psychologist who was not involved in the rehabilitation process.

#### Statistical considerations

##### Sample size

We calculated the required case number for paired unilateral *t* tests for pre-post comparisons. Due to the small time intervals between the measurements, a small-to-medium effect size of 0.25 with an α-error probability of 0.05 is expected. An expected correlation of the measured values of at least 0.60 requires a power of 0.80. The power analysis revealed a sample size of 162 patients, *N* = 81 per center. Assuming a drop-out rate of 20%, as usually expected in a clinical trial, 92 patients per center would need to be enrolled.

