**Methods/design:**

The aim of the study is to examine the effectiveness and efficiency of our new ICF (International Classification of Functioning, Disability and Health)-based rehabilitation for thermal injuries. Because of ethical reasons, we have chosen a prospective non-randomized design, which takes place at two different rehabilitation centers. At center A, a newly developed ICF-based rehabilitation program was established; at rehabilitation center B, a well-established rehabilitation program has existed for 20 years and is used as reference. The *primary research question* addresses the “Pre-post comparison of the physical and psychological outcome measurements,” *secondary question I* looks at the “Examination of the non-inferiority of the new treatment concept with the established concept,” and *secondary question II* is the “Analysis of the rehabilitation process based on the rehabilitation cycle.”

Only patients of the two burn rehabilitation centers who are insured by workers’ compensation will be asked to participate in this study to avoid outcome bias by insurance status. A physical examination (physical working capacity testing, grip strength, range of motion, and scar evaluation by Cutometer and Vancouver Scar Scale) and a standardized questionnaire battery (Burn Specific Health Scale-Brief , Short Form 36, Impact of Event Scale-Revised, the German version of the Symptom Checklist, the Freiburg Social Support Questionnaire, Patient/Client Satisfaction Questionnaire, Disabilities of the Arm, Shoulder and Hand, and Lower Extremity Functional Scale ) measure physical and psychological conditions. Data will be taken on admission, during stay, and on discharge of the rehabilitation program and at follow-up 3 and 12 months after discharge. A minimum of 162 participants will be enrolled in this clinical longitudinal, prospective, observational study.

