##### Statistical methods

Data will be collected continuously. For the statistical analysis, data will be checked for a normal distribution. Data are expressed by means with standard deviations and medians with interquartile range as appropriate. Categorical variables will be expressed as percentages.

Pre-post comparison (T1–T2) of the outcome measures will be tested by paired one-sided *t* tests. Longitudinal treatment effects will be tested by paired one-sided *t* tests between T1 and T3 and between T1 and T4.

The non-inferiority between the two centers will be proved with a power of 0.80 if differences are smaller than 0.4 standard deviation. Since randomized assignment to the centers is not possible, a potential selection bias between the samples will be matched by age, gender, TBSA, ABSI, and inhalation trauma. In case of an imbalance of the two samples, the analysis will be made along the procedure of propensity score matching.

A descriptive analysis of the patients’ rehabilitation goals and their linkage to the ICF categories will be performed. Patients’ and therapists’ assessments of goal achievement will be compared. The mean frequency of changing goals during the course of rehabilitation will be obtained. Furthermore, patients’ satisfaction with rehabilitation will be assessed with a qualitative interview, which will be evaluated by content, and the results of the CSQ-8 will be expressed by means and standard deviations.

The statistical evaluation will be carried out in cooperation with the statistician who participated in the design of the study (see Acknowledgements).

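### The enrolment target of 92 per centre does not follow from 81 evaluable patients and 20% drop-out; it covers just under 12%, and 20% needs 102.

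*Protocol article*

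**What the plan says.** The Sample size section of the protocol article sets out the calculation in three steps.

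- Test: "We calculated the required case number for paired unilateral *t* tests for pre-post comparisons".
- Inputs: "a small-to-medium effect size of 0.25 with an α-error probability of 0.05 is expected", followed by "An expected correlation of the measured values of at least 0.60 requires a power of 0.80".
- Result: "The power analysis revealed a sample size of 162 patients, *N* = 81 per center".

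The drop-out allowance comes next: "Assuming a drop-out rate of 20%, as usually expected in a clinical trial, 92 patients per center would need to be enrolled". This makes 184 patients in total. The article gives no other drop-out rate and no other inflation rule.

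Two other places depend on these numbers. The abstract (Methods/design) says: "A minimum of 162 participants will be enrolled in this clinical longitudinal, prospective, observational study". The Statistical methods section makes a separate power claim for the comparison of centres: "The non-inferiority between the two centers will be proved with a power of 0.80 if differences are smaller than 0.4 standard deviation".

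**The concern.** If 81 patients per centre must be evaluable and one in five is lost, 92 cannot be enough: 80% of 92 is below 74. The stated power of 0.80 would then not hold at the stated enrolment and drop-out, either for a pre-post test within a centre or for the non-inferiority comparison.

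The article also leaves three enrolment figures in play: 162 in the abstract, 184 from the sample-size section, and 204 implied by its own 20%. This matters in practice because the section on interim analysis and stopping rules makes a significant failure to reach the planned sample size a reason to terminate the study. The planned size therefore has to be a single, correct number. Drop-out also bears on the primary question directly, since that question includes comparisons at 3 and 12 months after discharge.

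**Working it through.** **Inputs.** From Sample size: one-sided paired t test, effect size 0.25, correlation 0.60, alpha 0.05, power 0.80, 81 per centre, drop-out 20%, enrolment 92 per centre. From Statistical methods: non-inferiority margin 0.4 SD, power 0.80. No alpha is stated for the non-inferiority test.

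**Step 1: reproduce the 81.** Take 0.25 as the mean change in units of the SD at one time point. In units of the SD of the differences it becomes

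dz = 0.25 / √(2 × (1 − 0.60)) = 0.2795.

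With the noncentral t distribution and one-sided alpha 0.05, power is 0.798 at n = 80 and 0.802 at n = 81. So 81 is exactly the smallest number that reaches 0.80 in one centre, and it contains no reserve for drop-out. (Using dz = 0.25 directly would need 101, which does not match the article.)

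**Step 2: apply the drop-out.**

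- Correct inflation: 81 / (1 − 0.20) = 101.25, so 102 per centre, 204 in total. Inflating the total of 162 directly gives 202.5, so 203.
- Common shortcut: 81 × 1.20 = 97.2, so 98.
- Stated: 92. Neither rule gives it.
- Drop-out that 92 can absorb: 1 − 81/92 = 0.1196, just under 12%.
- Evaluable at 20% loss: 92 × 0.80 = 73.6, so 73 to 74 per centre.

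**Step 3: power at the numbers that remain.** The pre-post column uses dz = 0.2795 and one-sided alpha 0.05. The non-inferiority columns use a two-sample t test with margin 0.4 SD and true difference 0. Because the article gives no alpha for that test, both usual levels are shown.

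| Evaluable per centre | How it arises | Pre-post, one centre | Non-inferiority, one-sided 0.05 | Non-inferiority, one-sided 0.025 |
|---|---|---|---|---|
| 81 | as planned | 0.8022 | 0.8133 | 0.7158 |
| 74 | 92 enrolled, 20% lost, rounded up | 0.7695 | 0.7814 | 0.6762 |
| 73 | 92 enrolled, 20% lost, rounded down | 0.7645 | 0.7765 | 0.6702 |
| 65 | 162 enrolled in total, 20% lost (81 × 0.80 = 64.8) | 0.7206 | 0.7335 | 0.6192 |

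With 81 per centre, the article's claim of 0.80 for non-inferiority is met at one-sided 0.05 (0.8133) but not at 0.025 (0.7158). One-sided 0.05 is therefore the level consistent with the article, though it remains an assumption.

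**Step 4: the pooled reading.** If the pre-post test combines both centres, 2 × 73 = 146 completers give power of about 0.96.

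**The case against.** No reading of the section yields 92, so the arithmetic itself cannot be defended. The case on the other side is about consequence.

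- **Pooling.** Statistical methods does not say whether the paired tests are run per centre or over both centres, and the primary question is not split by centre. On a pooled test, power stays near 0.96 and the primary question is not at risk. This stands as a limit on the consequence. It does not make 92 correct: 81 is exactly the one-centre requirement, and a comparison between centres cannot be pooled.
- **Size of the loss.** Three to four points of power is modest, and the correlation of 0.60 is given as a lower bound. At a correlation of 0.64, 73 patients already give 0.802. This also stands, but a sample size justified at 0.60 has to hold at 0.60.
- **Non-inferiority alpha.** The figure of 0.78 rests on an alpha that the article does not state. At one-sided 0.025, even the full 81 would give only 0.72, so most of that gap would have nothing to do with drop-out. The planned matching could also reduce the number analysed, which these figures ignore. Any restated non-inferiority power should therefore name its assumptions.
- **The abstract.** A minimum of 162 is a floor and does not contradict enrolling 184. No section plans to stop at 162, so the row for 65 per centre is a worst case. What remains is that the abstract gives the evaluable number as an enrolment number.

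**Conclusion.** The concern holds. The stated enrolment of 92 per centre contradicts the article's own 81 evaluable patients and 20% drop-out. The figure that follows from them is 102 per centre, so the target is 10 short per centre and 20 short in total.

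At the stated 20% loss, pre-post power within a centre is about 0.76 to 0.77, assuming a correlation of 0.60. Non-inferiority power is about 0.78, assuming one-sided alpha 0.05, no true difference and no further loss through matching. Both fall short of the 0.80 claimed. A pre-post test pooled over the two centres would not be underpowered. The effect on power is modest, but the sample-size statement is wrong as written and should be corrected.

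**What to change.** Correct the drop-out sentence in Sample size in one of two ways:

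1. State 102 per centre (204 in total) for 20% drop-out.
2. Keep 92 per centre (184 in total), say that it covers a drop-out of just under 12%, and report what 20% would leave: 73 evaluable per centre, with power of about 0.76 for the per-centre pre-post test and about 0.78 for non-inferiority at one-sided alpha 0.05 and a true difference of 0. Because the article itself expects 20%, restating the allowance as 12% without this disclosure would not be enough.

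In the abstract, describe 162 as the number of evaluable patients and give the enrolment target separately, so that the termination criterion for missed recruitment refers to one number.

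The cost is one sentence in each place. The second option needs no extra patients but reports slightly lower power; the first needs 20 more patients than the present target (204 − 184).

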##### Interim analysis and stopping rules

After 2 years as a first milestone, a preliminary evaluation is planned. Termination of the study is considered in the event that severe side effects of the rehabilitation are shown. This includes both physical and psychological aspects. A significant failure in reaching the planned sample size is also defined as a termination criterion.

##### Randomization

No randomization is planned because of ethical reasons. The assignment of a patient to center A or B depends solely on the proximity of the patient’s hometown and the capacity of the center.

##### Statistical methods

Data will be collected continuously. For the statistical analysis, data will be checked for a normal distribution. Data are expressed by means with standard deviations and medians with interquartile range as appropriate. Categorical variables will be expressed as percentages.

Pre-post comparison (T1–T2) of the outcome measures will be tested by paired one-sided *t* tests. Longitudinal treatment effects will be tested by paired one-sided *t* tests between T1 and T3 and between T1 and T4.

The non-inferiority between the two centers will be proved with a power of 0.80 if differences are smaller than 0.4 standard deviation. Since randomized assignment to the centers is not possible, a potential selection bias between the samples will be matched by age, gender, TBSA, ABSI, and inhalation trauma. In case of an imbalance of the two samples, the analysis will be made along the procedure of propensity score matching.

A descriptive analysis of the patients’ rehabilitation goals and their linkage to the ICF categories will be performed. Patients’ and therapists’ assessments of goal achievement will be compared. The mean frequency of changing goals during the course of rehabilitation will be obtained. Furthermore, patients’ satisfaction with rehabilitation will be assessed with a qualitative interview, which will be evaluated by content, and the results of the CSQ-8 will be expressed by means and standard deviations.

The statistical evaluation will be carried out in cooperation with the statistician who participated in the design of the study (see Acknowledgements).

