#### Primary research question

Do the patients benefit from the rehabilitation program regarding their physical and psychological health conditions? Furthermore, are the changes steady after rehabilitation?

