##### Hypotheses

The alternative hypothesis (H1) is as follows:
Physical and psychological outcome measures are enhanced after burn rehabilitation compared to measures before rehabilitation.Physical and psychological outcome measures are enhanced 3 and 12 months after rehabilitation compared to measures before rehabilitation.

The null hypothesis (H0) is as follows:
Physical and psychological measurements are not improved after the burn rehabilitation compared to measures before rehabilitation.Physical and psychological outcome measures are not enhanced 3 and 12 months after rehabilitation compared to measures before rehabilitation.

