### Outcome measures

The types of outcome measures used to collect participant data are listed in Table 3.

**Table 3 Tab3:** Data collected at baseline (T1) and follow-up

	T1 Admission	Weekly	T2 Discharge	T3 3 months after discharge	T4 12 months after discharge
Physical outcome measures					
PWC 150	X		X	X	X
VSS	X		X	X	X
ROM of the large joints	X		X	X	X
Cutometer	X		X	X	X
Grip strength	X		X	X	X
DASH	X		X	X	X
Muscle function	X		X	X	X
LEFS	X		X	X	X
Psychological outcome measures					
BSHS-B	X		X	X	X
SF-36	X		X	X	X
IES-R	X		X	X	X
SCL-K-9	X		X	X	X
F-SozU	X		X	X	X
CSQ-8			X	X	X
ICF-based rehabilitation goals	X	X			
Semi-structured interview			X		

*PWC* physical working capacity test, *VSS* Vancouver Scar Scale, *ROM* range of motion, *DASH* Disabilities of the Arm, Shoulder and Hand, *LEFS* Lower Extremity Functional Scale, *BSHS-B* Burn Specific Health Scale-Brief, *SF-36* Short Form Health Survey, *IES-R* Impact of Event Scale-Revised, *SCL-K-9* Symptom Checklist 9, *F-SozU* Freiburg Social Support Questionnaire, *CSQ-8* Patient/Client Satisfaction Questionnaire, *ICF* International Classification of Functioning, Disability and Health

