## Discussion

The primary focus of this study is to evaluate the rehabilitation program of two different burn rehabilitation centers. Since there is consensus in the burn literature that outcome is multidimensional for burn survivors, we included a broad spectrum of outcome parameters for the pre-post comparison. We chose the outcome measures along the ICF concepts of body function and structure (exercise capacity, muscle function, scar assessment), personal and environmental factors (mental health, social support), and activities and participation (simple activities, activities of daily living, return to work) in order to get a holistic view about the impact of burn injuries and the treatment necessities.

The instruments we chose are predominantly burn-specific (e.g., the BSHS-B) or frequently used in other burn injury studies (e.g., the SF-36 and IES-R) to enable better comparison with other studies. Instruments used for the evaluation of body function and structure are standard assessments such as the PWC, muscle function, and grip strength or commonly used instruments for scar assessment like the VSS und the Cutometer® MPA 580. The assessment will be conducted before and after the rehabilitation program and at two follow-up points (3 and 12 months after rehabilitation). The long follow-up period was chosen to prove the long-term effect of the rehabilitation program on the wellbeing of the patients. In the best case, patients will be enabled to fully participate again in their normal life in all aspects through the rehabilitation treatment. Since the complex multidisciplinary rehabilitation treatment is very strenuous for the patients as well as very cost intensive for the insurance, it is also essential to prove its effectiveness and quality to avoid unnecessary strain on the patients as well as unnecessary costs. After completion of the study, it is further planned to integrate the assessment instruments into clinical routine, if they prove to be relevant, and to provide these standardized documents to other interested rehabilitation facilities for burn injuries in Germany.

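### The primary hypothesis spans 13 measures and three comparisons (at least 39 one-sided tests) with no primary measure, time point or success rule, so the stated alpha and power describe one test and not the primary question

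*Protocol article*

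**What the plan says.** The primary research question is general: "Do the patients benefit from the rehabilitation program regarding their physical and psychological health conditions". The alternative hypothesis has two parts. The first is "Physical and psychological outcome measures are enhanced after burn rehabilitation compared to measures before rehabilitation". The second is "Physical and psychological outcome measures are enhanced 3 and 12 months after rehabilitation compared to measures before rehabilitation". Neither part says which measure decides, or whether one, several or all must improve.

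On the measures, the article states: "The types of outcome measures used to collect participant data are listed in Table 3". That table has eight physical measures (PWC 150, VSS, ROM, Cutometer, grip strength, DASH, muscle function, LEFS) and five psychological ones (BSHS-B, SF-36, IES-R, SCL-K-9, F-SozU) with values at T1, T2, T3 and T4. The CSQ-8 is listed too but has no admission value: "At discharge and after 3 and 12 months, patients are asked to complete the German version of the CSQ-8". It cannot enter a pre-post test.

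Under Statistical methods, "Pre-post comparison (T1–T2) of the outcome measures will be tested by paired one-sided" t tests, and "Longitudinal treatment effects will be tested by paired one-sided" t tests for T1 against T3 and T1 against T4. No significance level is given there. The Sample size section gives alpha 0.05, effect size 0.25, correlation 0.60 and power 0.80 for paired one-sided t tests, leading to 162 patients, 81 per centre. The Discussion presents the breadth as intended: "we included a broad spectrum of outcome parameters for the pre-post comparison".

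**The concern.** A primary hypothesis that covers a whole battery needs either one deciding measure or a rule for combining results. Without either, two readings are open, and each has its own problem.

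- **Any measure counts.** One favourable result among many could be reported as benefit, and the decisive measure could be picked after the data are seen. The chance of at least one false positive then exceeds the single-test alpha.
- **All measures must improve.** Alpha is protected, but the power to succeed on all of them is lower than the power for one.

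In either case the alpha and power in the Sample size section describe a single test. The stake is the main conclusion, because the article says it aims to prove the effectiveness of the programme.

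**Working it through.** **1. The plan's own figure.** Inputs from Sample size: d = 0.25, correlation 0.60, one-sided alpha 0.05, power 0.80. The effect on the paired difference is dz = 0.25/√(2 × (1 − 0.60)) = 0.2795. Solving the one-sided paired t test gives n = 80.5, rounded up to 81, with power 0.802 at n = 81. The stated 81 per centre reproduces, and it is the size for one test. At n = 162 (both centres pooled, no dropout) the same test has power 0.971.

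**2. Number of tests.** 8 + 5 = 13 measures with a T1 value, times three comparisons (T1–T2, T1–T3, T1–T4), gives 39. This is a minimum. The article also describes nine BSHS-B subscales, eight SF-36 scales, two scar sites, two Cutometer parameters and grip in each hand. Testing each centre separately would double the count.

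**3. If any significant measure counts, each test at 0.05.** Under independence the family-wise error is 1 − 0.95^k:

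- k = 13: 1 − 0.95^13 = 0.487
- k = 39: 1 − 0.95^39 = 0.865

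The article gives no correlation between measures, so I assumed a common correlation ρ between the test statistics. With U standard normal, the error is 1 − E[Φ((1.645 − √ρ·U)/√(1 − ρ))^k].

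| ρ (assumed) | any of 13, T1–T2 | any of 39 |
|---|---|---|
| 0 | 0.487 | 0.865 |
| 0.3 | 0.357 | 0.584 |
| 0.5 | 0.281 | 0.434 |
| 0.7 | 0.206 | 0.296 |

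Full independence cannot hold across time points, because the three comparisons share the T1 value. If all visits correlate at 0.60 with equal variance, two change scores have covariance (1 − 0.6 − 0.6 + 0.6)σ² = 0.4σ² and variance 0.8σ² each, so they correlate at 0.5. A simulation with 0.5 between time points gave, for all 39 tests, 0.80 with independent measures, 0.63 with 0.3 between measures and 0.40 with 0.7. The 0.865 is therefore an upper figure.

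**4. If all 13 must improve at T1–T2.** With the same common-correlation model, when every measure truly has the planned effect:

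| ρ (assumed) | n = 81, power 0.80 each | n = 162 pooled, power 0.971 each |
|---|---|---|
| 0 | 0.80^13 = 0.055 | 0.971^13 = 0.683 |
| 0.3 | 0.223 | 0.761 |
| 0.5 | 0.341 | 0.813 |
| 0.7 | 0.469 | 0.865 |

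**5. What a later correction would cost.** Bonferroni over 13 tests (alpha 0.05/13 = 0.00385) leaves power 0.42 at n = 81 and 0.80 at n = 162. Over 39 tests (0.05/39 = 0.00128) it leaves 0.28 and 0.69.

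**The case against.** The strongest reply is that a statistical analysis plan may exist and may hold a multiplicity method, and an article need not repeat it. That is fair for the adjustment itself: nothing here shows that none is planned. It does not reach the main defect. The choice of primary measure and success rule defines the hypothesis and the sample size, both of which are set out in the article, and it is not normally left to an analysis plan.

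Three stronger readings are tempting and are not supported.

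- *Each of the 39 tests is stated to run at 0.05.* Statistical methods gives no level. The 0.05 comes from the Sample size section, and applying it to every test is a reasonable inference.
- *A chance improvement is likely.* For the discharge tests alone the probability stays below one half even under independence. For all 39 it exceeds one half only at weak to moderate correlation. What holds throughout is that it is well above 0.05.
- *Power is far too low if all must improve.* That is true at 81 patients in one centre. The article does not say that the pre-post tests are run by centre, and with the centres pooled and no dropout, joint power is near or above 0.80 once the measures are moderately correlated.

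The broad outcome set also has a stated rationale in the ICF framework. That justifies collecting the measures. It does not say which result answers the primary question.

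**Conclusion.** The point holds. The primary hypothesis covers 13 measures at three comparisons, and nothing in the article says which result, or what combination, counts as success. If any significant measure suffices at 0.05 each, the error rate is about 0.21 to 0.49 for discharge alone and 0.30 to 0.86 for all 39 tests, roughly four to seventeen times the stated alpha. These ranges rest on assumed correlations of 0.7 down to 0, and the conclusion is the same at every value tried. The power shortfall under an all-must-improve rule is conditional: 0.05 to 0.47 at n = 81, 0.68 to 0.87 at n = 162 without dropout. It needs correction before analysis because it concerns the study's main conclusion.

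**What to change.** Before analysis, state:

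1. **One primary measure with a defined score.** If the BSHS-B is chosen, the score must be specified, because the article describes nine subscales and no total.
2. **One primary comparison**, for example T1–T2, at one-sided 0.05.
3. **The analysis population**, pooled or by centre. Aim of study and Discussion speak of both centres, while Objective speaks of the new concept, so this choice has to be made openly.
4. **A complete fixed order for any further confirmatory tests**, each at one-sided 0.05, stopping at the first non-significant result. For example: one named physical measure at T1–T2, then the primary measure at T1–T3, the physical measure at T1–T3, the primary measure at T1–T4, the physical measure at T1–T4.
5. **All other measures** reported with effect sizes and confidence intervals and labelled supportive. Adjusting p-values separately within the physical and psychological domains would not control error across both domains or jointly with the sequence.

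Co-primary measures or an explicit all-or-any rule would also remove the ambiguity, but alpha or sample size would then have to be reworked.

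The cost is wording only. The primary test keeps n = 81 and power 0.80. The downside is that the remaining measures become secondary evidence, and later tests in the sequence can be claimed only if all earlier ones succeed.

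### The 3- and 12-month gains are tested by separate paired t tests, so with the plan's own drop-out they rest on returning patients only and on subsets that can differ by visit

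*Protocol article*

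**What the plan says.** All references are to the protocol article.

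- **Statistical methods**, discharge: "Pre-post comparison (T1–T2) of the outcome measures will be tested by paired one-sided" t tests.
- **Statistical methods**, follow-up: "Longitudinal treatment effects will be tested by paired one-sided" t "tests between T1 and T3 and between T1 and T4". These are two further tests, each on its own pair of visits.
- **Primary research question** and **Hypotheses**: besides benefit at discharge, the primary question asks whether the changes hold afterwards. Improvement over admission at 3 and 12 months is written into the alternative hypothesis.
- **Sample size**: the calculation rests on the same test ("We calculated the required case number for paired unilateral" t tests) and gives 81 patients per centre. It continues "Assuming a drop-out rate of 20" per cent and arrives at 92 enrolled per centre. The drop-out rate is not tied to any visit and is used only to raise enrolment.

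The article names no model that uses patients with incomplete follow-up, no imputation, and no analysis set common to the visits.

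**The concern.** A paired t test cannot use a patient who lacks one of the two values. The T1–T3 test drops everyone not seen at 3 months, and the T1–T4 test drops everyone not seen at 12 months. What those patients showed at admission and discharge does not enter the follow-up estimate.

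Two things are at stake.

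- **Comparability.** Whether the changes are steady can be read from the T2, T3 and T4 gains only if they describe the same patients. Under separate tests with attrition, a gain that seems to last, or to fade, may partly reflect who came back.
- **Bias.** If returning is related to how much a patient changed, the gain among returners is not the gain in the enrolled population. The primary comparison is within patients, without a randomised control, so no parallel arm offsets this.

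**Working it through.** **1. The plan's own figure.** Inputs from Sample size: effect 0.25 SD, one-sided alpha 0.05, correlation 0.60, power 0.80. The standardised paired difference is 0.25 / √(2 × (1 − 0.60)) = 0.2795. The exact paired t calculation gives n = 81 (power 0.802), as stated per centre. The planned effect of 0.25 SD is therefore in units of the outcome SD, and the same unit is used below.

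**2. Pairs left.** Apply the 20% to one follow-up visit. This is an assumption, since the article assigns it to none.

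- Per centre: 92 × 0.80 = 73.6, about 74 pairs; power 0.77.
- Both centres: 184 × 0.80 = 147.2, about 147 pairs; power 0.96 if pooled.

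**3. Size of the bias.** Let R be the mean gain of returners and N that of non-returners.

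- All-patient gain = 0.80R + 0.20N
- Completer gain = R
- Difference = R − (0.80R + 0.20N) = 0.20 × (R − N)

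The article gives no value for R − N. Assumed values:

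| R − N (SD) | Bias (SD) | Share of planned 0.25 SD |
|---|---|---|
| 0.25 | 0.05 | 20% |
| 0.50 | 0.10 | 40% |

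The sign follows R − N: positive if returners gained more, negative if they gained less.

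**4. When bias arises, and what a model recovers.** Simulation with assumed inputs: outcome SD 1, all correlations 0.6, true gain 0.25 SD at T2 and T4, 20% missing at T4. The comparison estimate regresses T4 on T1 and T2 in returners and averages the prediction over all patients; it stands in for a mixed model.

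| What the chance of returning depends on | Log-odds per outcome SD | Completer gain | Estimate using all T1 and T2 |
|---|---|---|---|
| Observed T1–T2 change | 0 (random loss) | 0.25 | 0.25 |
| Observed T1–T2 change | 0.5 | 0.29 | 0.25 |
| Observed T1–T2 change | 1.0 | 0.32 | 0.25 |
| Observed T1–T2 change | 1.5 | 0.35 | 0.25 |
| T2 level only | 0.5 to 1.5 | 0.25 | 0.25 |

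Loss related to the change produces bias. Loss related only to the T2 level does not, under equal correlations. The rows with bias are upward because the simulation let patients with larger early gains return more often; reversing that would reverse the sign.

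**5. Precision a model would recover.** With all correlations 0.6, Var(T4 − T1) = 2 × (1 − 0.6) = 0.8. The regression of T4 on T1 and T2 has coefficients 0.6/1.6 = 0.375 each and residual variance 1 − 2 × 0.375 × 0.6 = 0.55, leaving 0.8 − 0.55 = 0.25 estimated from everyone.

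- Variance of the estimated gain ≈ 0.25/92 + 0.55/73.6 = 0.0102
- Effective n ≈ 0.8/0.0102, about 78.5

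That is about 5 patients more than 73.6 per centre.

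**The case against.** **Missing-data handling belongs in the analysis plan.** The article names a test, not an analysis set, and a paired t test can be run on imputed data. An unseen analysis plan may provide for that. This limits the point but does not remove it: the article chooses the estimator for part of its primary question, and as written that estimator uses only complete pairs. The choice also matches the sample-size basis, which reproduces exactly; that supports the planned number but does not address attrition.

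**Bias is not certain and its direction is unknown.** This stands. A reader might infer that the analysis will overstate lasting benefit because patients who do badly stay away. Nothing in the article shows who will be lost. Nor is it right that any link between loss and patients' condition causes bias: the T2-level rows show none.

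**The size is assumed, and a model does not recover all of it.** This also stands. The differences in gain are illustrative, and the 20% is placed at one visit by assumption. The full recovery to 0.25 occurs because loss was made to depend on an observed change. If patients are lost for reasons not visible in their earlier values, some or all of the bias remains.

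**Power.** A reader might compare about 74 pairs with 92 and see a large loss. The 92 already includes an allowance for drop-out; the requirement is 81. The shortfall below 81 arises because 92 does not allow for 20% loss (81/0.80 = 101.25, so 102), which is a separate matter.

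**T1–T2.** The stay is planned for 3 weeks with individual extension, so later attrition does not touch this test. The concern is about T3 and T4.

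**Conclusion.** The point holds for the 3- and 12-month contrasts. The stated method estimates those gains in returners only, and the T2, T3 and T4 gains can rest on different subsets. For the enrolled population the follow-up gains are biased if loss is related to the change, by 0.20 times the returner–non-returner difference: 0.05 to 0.10 SD for assumed differences of 0.25 to 0.5 SD, against a planned 0.25 SD. This rests on 20% being lost at the visit concerned.

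The article does not support saying that bias will occur, that it will favour the programme, or that a mixed model would remove it whatever the cause of loss. Precision is a minor matter: power 0.77 per centre and 0.96 pooled, with only a few patients' worth of information to regain. The case for change rests on comparability across visits and protection against loss that earlier values can explain.

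**What to change.** For the continuous outcomes, fit one linear mixed model for repeated measures per outcome to all available T1, T2, T3 and T4 values, with visit as a category and an unstructured covariance. Take the T3−T1 and T4−T1 contrasts from it, and T2−T1 as well for comparability, one-sided as planned.

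If centre and centre-by-visit terms are included, define the overall contrast in advance as the enrolment-weighted average over the centres. List the outcomes that are to be treated as continuous; the 0 to 5 muscle function rating, for example, is ordinal.

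Keep the paired t tests as a complete-case sensitivity analysis. State the limit in the plan: the model removes bias only when loss depends on observed values (missing at random).

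The cost is a little more analysis work on data already scheduled. No visit, measurement or patient is added.
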